### Criteria for discontinuing or modifying allocated interventions {11b}

Participants may discontinue or have their allocated intervention modified during the trial based on the following criteria:Adverse events or safety concerns. The occurrence of adverse events related to the intervention, such as visual discomfort, eye strain, or other unexpected side effects that compromise the participants’ safety or well-being.Non-compliance with protocol. Persistent non-compliance with the study protocol, including failure to adhere to the prescribed use of DIST or participation in required follow-up visits, despite reasonable efforts to ensure adherence.Participant or guardian decision. Withdrawal of consent by the participant or their guardian for any reason, including personal preferences or perceived lack of benefit from the intervention.Investigator’s discretion. Determination by the investigator that continuing the intervention is not in the participant’s best interest, based on clinical judgment or unforeseen circumstances affecting the study’s integrity.

Participants who discontinue or modify their allocated interventions will remain in the study unless they explicitly request withdrawal. Their data will be included in the Intention-to-Treat analysis to ensure a comprehensive evaluation of the intervention’s efficacy.

### Strategies to improve adherence to interventions {11c}

To enhance participant adherence, each participant will be assigned a dedicated research assistant who will maintain regular contact with the participant’s family through a dedicated WeChat group. The research assistants will offer support by addressing any questions, troubleshooting equipment issues, and sending reminders to ensure timely completion of the intervention and follow-up activities. For experimental groups using DIST, the research team will monitor the device’s usage through backend records once a week to verify adherence to the required usage duration. If any irregular usage patterns are detected, the research assistants will promptly inform the participant’s family and provide personalized guidance to ensure consistent adherence.

### Relevant concomitant care permitted or prohibited during the trial {11d}

Clearly defining permitted and prohibited concomitant care is essential to preserving the integrity of its intervention, protecting participant health and minimising confounding factors.

Permitted concomitant care primarily includes recommendations for healthy visual habits, such as ensuring appropriate reading distance, adequate lighting, and regular outdoor activities. These practices are permitted and encouraged, as they align with standard myopia prevention guidelines.

In contrast, the following are strictly prohibited as concomitant care. First are alternative myopia control interventions. Participants are not allowed to use other myopia control strategies, such as atropine eye drops or other optical interventions (e.g., defocus lenses), during the trial period. Second are experimental therapies. Enrollment in other clinical trials or use of investigational devices or drugs targeting myopia management is prohibited to avoid confounding effects. Last but most important are device modifications. Any unauthorized adjustments or modifications to the DIST device or its usage protocol are also strictly prohibited.

To ensure adherence, all concomitant care received by participants must be reported to the research team and documented during follow-up visits. Any potential impact on study outcomes will be evaluated, and all such data will be recorded in the case report forms (CRFs). Participants and their families will be instructed to notify the study team of any changes in care or new treatments initiated during the trial.

### Provisions for post-trial care {30}

All interventions in our study are considered safe, with no anticipated harm under normal circumstances. However, in the unlikely event that a participant sustains an injury or adverse effect related to the study interventions, the research sponsor will provide comprehensive post-trial care. This includes covering all associated medical expenses and providing appropriate financial compensation based on an assessment conducted by a qualified ophthalmologist.

### Outcomes {12}

#### Primary outcome

##### Proportion of myopia onset

Myopia onset is defined as cycloplegic spherical equivalent refractive error of at least − 0.50D in either eye over 1 year, in accordance with the Refractive Error Study in Children. This outcome assesses the effectiveness of the DIST intervention in delaying the onset of myopia in pre-myopic children.

#### Secondary outcomes

*Proportion of fast myopia progressors*: Fast myopia progression is defined as a spherical equivalent myopic shift of at least 0.50 D over 1 year. This outcome helps assess whether the DIST intervention can reduce the incidence of rapid myopic progression.*Changes in spherical equivalent progression (D) at each follow-up point*: This outcome measures the change in spherical equivalent refractive error at each follow-up, serving as a direct indicator of the effect of DIST on refractive progression. It complements the primary outcome by providing additional data on the intervention’s ability to control myopia progression. Ocular parameters of the right eye will be used for analysis to ensure consistency.*Changes in axial length (AL) (mm) at each follow-up point*: AL is a key marker of myopia progression. Monitoring changes in AL will reveal the impact of DIST on ocular growth, which is crucial in myopia development. This outcome provides biological evidence that complements refractive error data, helping to understand how DIST may influence eye structure.

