### Participant timeline {13}

Screening, baseline, and follow-up time points throughout the study followed a pre-determined schedule, as described in Table 1.

**Table 1 Tab1:** Timeline of screening, enrollment, and assessments

	Study period				
Procedure	Screening period	Enrolment	Post-assessments		
			3 months (± 14 days)	6 months (± 14 days)	12 months (± 14 days)
Informed consent	X				
Inclusion/Exclusion criteria	X				
General information and relevant medical history	X				
Questionnaire survey		X	X	X	X
Visual acuity(distant)	X		X	X	X
Sub-pupil computer refraction and cornea curvature	X		X	X	X
Sub-pupil subjective refraction	X		X	X	X
Slit-lamp examination	X		X	X	X
Fundus examination	X		X	X	X
Tonometry		X		X	X
Axial length		X	X	X	X
OCT		X		X	X
Paralyze the ciliary muscle		X		X	X
Computer refraction and cornea curvature^a^		X		X	X
Subjective refraction^a^		X		X	X

*OCT* optical coherence tomography

^a^With cycloplegia

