## Data collection and management

### Plans for assessment and collection of outcomes {18a}

At baseline and during each follow-up, researchers will provide paper-based questionnaires for guardians to complete, and the results will be entered into a spreadsheet for analysis. All other clinical assessments will be performed by experienced clinicians using relevant measuring instruments (as specified in item 12). Measurements will be repeated to ensure the reliability and validity of the data collection. Meanwhile, patients’ general information, medical history, baseline and follow-up results, adverse event reports, and trial summaries will be recorded in the CRFs by researchers on time. All researchers and clinicians will undergo training on participant recruitment, assessment, intervention, and data backup before participating in the study.

Cycloplegic autorefraction will be performed using the Topcon KR800 autorefractor unit following the cycloplegia regimen of 1% cyclopentolate (Cyclogyl, AlconConvreur). The procedure involves administering two drops of 1% cyclopentolate separated by a 5-min interval, followed by a 30-min resting period after the final instillation. Complete cycloplegia is confirmed by the absence of fluctuation in retinoscopy findings under cycloplegic conditions in children or by performing autorefraction combined with careful subjective refraction. Spherical equivalent is calculated as spherical power plus half of the cylinder power. Cycloplegic measurements will be performed at baseline, the 6-month follow-up, and the 12-month follow-up to assess the primary outcome.

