## Statistical methods

### Statistical methods for primary and secondary outcomes {20a}

Analysis of primary outcomeIn this participant-based study, the primary outcome is the proportion of myopia onset. This outcome is measured as a binary (nominal) variable. Participants are classified as either having experienced the onset of myopia (Yes) or not (No), based on whether their cycloplegic spherical equivalent refractive error reaches or exceeds − 0.50 D in either eye at the 1-year follow-up. This is a single endpoint measure, assessed once at the end of the 1-year follow-up period. It provides a proportion of participants who experience the onset of myopia. To test the effectiveness of DIST on the primary outcomes, logistic regression including trend analysis will be used, which can both examine the overall relationship and detect potential trends related to different treatments. In addition, covariates such as baseline spherical equivalent refractive error, age, gender, and study group (Intervention vs. Control) will be included to ensure a parsimonious logistic regression model while controlling for factors known to influence myopia onset and progression.The primary analysis will be conducted on the ITT population, which is defined as all randomized participants with at least one post-baseline measurement. For all analyses, the underlying model assumptions will be rigorously evaluated. For instance, when applying logistic regression to assess the binary primary outcome, we will verify the linearity of the logit for continuous covariates using methods such as the Box–Tidwell test, assess multicollinearity via variance inflation factors (VIF), and examine residuals and influence statistics (e.g., Cook’s distance) to identify any influential outliers. Missing data will be addressed using multiple imputations by chained equations under the assumption of data missing at random (MAR), with sensitivity analyses planned to assess the impact of outliers, nonadherence, and loss to follow-up.Analysis of secondary outcomesThe secondary outcomes are intended to capture aspects of the intervention effect that are not fully reflected by the primary outcome. For example, even if the primary outcome (myopia onset) does not show a statistically significant difference, significant changes in spherical equivalent or axial length may still be observed, thereby indicating a potential benefit of the intervention in slowing myopia progression.For the three secondary outcomes: (1) the proportion of fast progressors over 1 year, (2) changes in spherical equivalent progression, and (3) changes in AL (mm) at each follow-up point, the following statistical procedures will be employed:Proportion of fast progressors (binary outcome)This endpoint will be analyzed using logistic regression. The model will estimate the odds of being classified as a fast progressor over 1 year, comparing the intervention group to the control group. Covariates to be included in the model are baseline spherical equivalent refractive error (continuous), age (continuous), and gender (categorical), as these factors have been shown in prior research to influence myopia progression. The study group (intervention vs. control) will be the primary factor of interest. These covariates are selected based on their theoretical relevance and empirical support, ensuring a parsimonious model that controls for potential confounding without overfitting.Changes in spherical equivalent progression (continuous outcome)The change in spherical equivalent progression over time will be analyzed using a repeated measures mixed-effects model. This model will account for within-subject correlations across multiple follow-up points and will include fixed effects for the treatment group, time (as a categorical or continuous variable depending on the observed pattern), and the interaction between treatment and time. Baseline spherical equivalent refractive error, age, and gender will be included as covariates to adjust for initial differences and known predictors of refractive change. The rationale for these covariates is their established association with myopia progression, ensuring that the model is both explanatory and parsimonious. Model selection procedures, such as stepwise backward elimination based on the Akaike Information Criterion (AIC) or likelihood ratio tests, will be applied to refine the final model.Changes in AL (mm)Similar to the spherical equivalent endpoint, changes in axial length (measured in mm) at each follow-up will be analyzed using a repeated measures mixed-effects model or an analysis of covariance (ANCOVA) for longitudinal data. The model will include fixed effects for treatment, time, and their interaction. Covariates will include baseline axial length, baseline spherical equivalent, age, and gender. These factors are chosen because they are known to influence ocular growth and, consequently, axial elongation. As with the other endpoints, a parsimonious model will be achieved by using stepwise selection methods or likelihood ratio tests to retain only covariates that contribute significantly to explaining the variation in axial length change.The results of these analyses will be presented as adjusted odds ratios with 95% confidence intervals for the binary outcome and as least-squares means (LSMEANS) with standard errors for the continuous outcomes. In addition, p-values will be reported to assess the statistical significance of the observed differences between intervention groups.Analysis of exploratory outcomesTime-to-myopia onset analysisFor comparing the time to myopia onset (time-to-event outcome) among 3 treatment groups, we all create a number-at-risk table and use the Kaplan–Meier method to estimate survival curves, followed by the log-rank test to assess differences statistically.Myopia onset associationsA logistic regression model will be built with myopia onset as the dependent variable and near-work duration, device usage duration, and confounding factors as independent variables. The near-work duration was derived from the near-work log cards and questionnaires, with the daily averages taken for analysis. Odds ratio (OR) and its 95% confidence interval will be estimated to determine associations while controlling for confounding.Dose–response relationship analysisWe will group near work and device usage durations (e.g., by quartiles). Use the Cochrance–Armitage trend test to analyze if there’s a dose–response relationship. Curve fitting (such as polynomial regression) can also be used to further explore the non-linear relationship between them.Choroidal thickness changesFor exploring changes in choroidal thickness during different follow-up periods among three groups, repeated measures analysis of variance (ANOVA) will be used. If significant effects are found, post hoc tests (like Bonferroni or Tukey’s) will determine specific differences.

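### Spherical-equivalent change is defined at every follow-up, but the 3-month visit has no cycloplegic refraction to set against the cycloplegic baseline

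*Protocol article*

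**What the plan says.** Under Secondary outcomes, the protocol article describes SE change thus: "This outcome measures the change in spherical equivalent refractive error at each follow-up". It names the eye, "Ocular parameters of the right eye will be used for analysis to ensure consistency", but not whether the refraction is cycloplegic.

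Table 1 (Participant timeline {13}) sets follow-ups at 3, 6 and 12 months. The row "Paralyze the ciliary muscle" and the two refraction rows footnoted "With cycloplegia" are marked at enrolment, 6 and 12 months and are blank at 3 months. The section on assessment and collection of outcomes {18a} gives the same schedule in prose: "Cycloplegic measurements will be performed at baseline, the 6-month follow-up, and the 12-month follow-up to assess the primary outcome". At 3 months the only refractions are the small-pupil rows, such as "Sub-pupil computer refraction and cornea curvature", which are also marked at screening, 6 and 12 months.

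Statistical methods {20a} analyses SE change in a repeated-measures mixed model with group, time and their interaction, adjusted for baseline SE. Time may be categorical or continuous, depending on the pattern seen. Nothing there excludes the 3-month visit or says which refraction series is used.

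**The concern.** The outcome asks for a value at a visit where the measurement behind it is not taken. Filling the 3-month cell with what is available means subtracting a cycloplegic baseline from a reading in which accommodation is still active.

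This matters more here than in most refractive trials. The Abstract and the Intervention description {11a} present the device as a way of reducing accommodative stress. If it changes accommodative tone, a non-cycloplegic reading could show an arm difference without any difference in cycloplegic refraction. A time effect in the model removes an offset common to all arms, not one that differs by arm.

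The reading may also travel beyond 3 months. Section {20a} admits to the intention-to-treat set any randomised child with at least one post-baseline measurement, and section {20c} carries the last observation forward. A child lost after the 3-month visit has no post-baseline cycloplegic refraction.

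**Working it through.** The plan states no figure on this point, so there is none to reproduce. The check sets the sections side by side and then traces what a literal reading does.

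**1. Schedule (Table 1, confirmed in {18a})**

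| Refraction | Screening | Enrolment | 3 mo | 6 mo | 12 mo |
|---|---|---|---|---|---|
| Small pupil (non-cycloplegic) | yes | no | yes | yes | yes |
| Cycloplegic | no | yes | no | yes | yes |

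Table and prose agree, so the blank at 3 months is not an extraction fault. Cycloplegic SE exists at two of three follow-ups.

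**2. Which condition SE carries.** Wherever the protocol names one, it is cycloplegic: the SE inclusion criterion in {10}, the primary outcome in {12}, and {18a}, where SE is defined within the cycloplegic autorefraction paragraph. The baseline SE is therefore most naturally the cycloplegic one.

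**3. Contrast within the protocol.** Choroidal thickness is also not measured at 3 months, and its outcome definition is limited to 6 and 12 months. SE change has no such limit.

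**4. What a literal 3-month value contains.** Let the offset be the non-cycloplegic minus the cycloplegic reading.

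- Within an arm: apparent change = true change + offset.
- Between arms: apparent difference = true difference + (offset in device arm − offset in control arm).

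A common offset cancels between arms but distorts the time course. An offset that differs by arm enters the contrast one for one.

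**5. Illustration, on assumed values only.** Assume linear true change of −0.50 D per year: −0.125 D at 3 months, −0.25 D at 6 and −0.50 D at 12. Assume offsets of −0.25, −0.50 or −1.00 D.

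- −0.125 − 0.25 = −0.375 D
- −0.125 − 0.50 = −0.625 D
- −0.125 − 1.00 = −1.125 D

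Each apparent 3-month change is more myopic than the 6-month value of −0.25 D, a false reversal. At this rate, any myopic offset larger than 0.25 − 0.125 = 0.125 D produces one. With true change from −0.25 to −0.75 D per year, the apparent 3-month change runs from −0.0625 − 0.25 = −0.31 D to −0.1875 − 1.00 = −1.19 D.

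Spread also grows. If the offset varies between children independently of true change, the SD ratio is √(SD_change² + SD_offset²)/SD_change. For assumed SDs of change of 0.3 to 0.5 D and of offset of 0.25 to 0.5 D, it runs from √(0.5² + 0.25²)/0.5 = 1.12 to √(0.3² + 0.5²)/0.3 = 1.94.

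**6. Carry-forward.** For a child last seen at 3 months, the value carried to 12 months is either the cycloplegic baseline or the non-cycloplegic 3-month reading; the protocol does not say which. The planned dropout of 20% is 0.20 × 64 = 12.8 children per arm over the year. Those last refracted at 3 months are an unknown part of that.

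**The case against.** The strongest reply is that the protocol nowhere states that the two kinds of reading are combined. Two clean readings are open. SE may be cycloplegic throughout, with the 3-month value absent by design; or the small-pupil series from screening, 3, 6 and 12 months may be used as a like-for-like series of its own. The mixed model in {20a} speaks of several follow-up points, which 6 and 12 months satisfy. In the Abstract and in {20a} the phrase about follow-up points comes after axial length and need not govern SE, so the requirement rests clearly on the Secondary outcomes section alone.

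This stands in part. A reader might infer that the plan mixes the series outright; the documents do not say so. But the first reading contradicts the outcome as defined, and the second is never stated and departs from the only condition named for SE.

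It is also fair that the dioptre figures above are assumptions, that a common offset cancels between arms, and that distortion of a fitted slope arises only if time is continuous. A reader might set the offset against the 0.50 D fast-progression threshold. That endpoint is a one-year shift, and observed one-year refraction is available under cycloplegia, so the comparison misleads.

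A reader might further infer from the schedule that Kaplan–Meier curves "followed by the log-rank test to assess differences statistically" are wrong because onset can be detected only at 6 or 12 months. The documents do not support that as an error. All arms share one visit schedule, so the comparison remains valid with tied times; the outcome is exploratory, and an interval-censored model would be a preference.

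**Conclusion.** The outcome definition and the measurement schedule conflict. Read literally, the 3-month SE change compares a non-cycloplegic reading with a cycloplegic baseline. This rests on taking SE as cycloplegic, as the protocol does wherever it names a condition.

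The effect on the time course follows directly from any non-zero offset. Bias in the 3-month arm contrast is conditional on the device changing accommodation, and its size cannot be obtained from the documents. Carry-forward to 12 months is possible under {20c} but not stated.

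The reach is limited to one of three time points of one secondary outcome, plus any values carried from it. The primary outcome observed at 12 months, the SE change observed at 12 months, and axial length, which is measured at enrolment and all three follow-ups, are unaffected. The definition should be corrected before analysis; the point does not threaten the trial's main conclusion.

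**What to change.** In the Secondary outcomes section and in {20a}, define SE change as cycloplegic autorefraction at 6 and 12 months only. State that the 3-month non-cycloplegic reading enters neither the mixed model nor any carried-forward or imputed cycloplegic value. Report 3-month SE descriptively, as change from the non-cycloplegic screening reading. Keep 3, 6 and 12 months for axial length.

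The cost is one early time point of a secondary outcome, and an amendment, because this narrows a listed outcome in a running trial; the process in {25} applies. No new measurements are needed. Recruitment ended in September 2025, so scheduled 3-month visits were over by about the turn of that year and cycloplegia cannot be added to them. The last 12-month visits fall around September 2026, which leaves time to settle the wording before the analysis.
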